**Methods:**

We will perform a multicenter randomized controlled trial with two parallel groups. Within the 12-month inclusion period, we plan to recruit 158 adult patients with chronic pain during the initial stage of their interdisciplinary treatment program in one of the 6 participating centers. Participants will be randomly assigned to the standard treatment condition or to the enhanced treatment condition in which they will receive the AGRIPPA app. Patients will be monitored from the start of the treatment program until 12 months posttreatment. In our primary analysis, we will evaluate the difference over time of pain-related disability between the two conditions. Other outcome measures will include health-related quality of life, illness perceptions, pain self-efficacy, app system usage data, productivity loss, and health care expenses.

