### Study Setting

Six treatment facilities that provide IMPT programs participate in this study (2 hospital units and 4 rehabilitation clinics). All locations provide an interdisciplinary biopsychosocial-oriented treatment program to patients within the region, leading to a mixed rural and urban population throughout the Netherlands (ie, Arnhem, Eindhoven, Hoensbroek, Roermond, Maastricht, and Wijk aan Zee).

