#### Sample Size Calculation

The sample size calculation is based on a 2-factor repeated-measures analysis of variance with within-factor time (5 levels) and between-factor treatment (2 levels) conditions on the outcome variable PDI. We have set the α to .05, the power (1 – β) to .95, and assumed a moderate treatment effect (*f*=0.2). To account for the expected dependencies of patients within each of the 5 participating treatment locations, we applied the Donner et al [55] formula for the variance inflation factor, assuming an intracorrelation coefficient of 0.2 [56,57]. Furthermore, we corrected the analysis for an expected attrition of 20%, which is based on the average attrition of similar studies that used the PDI [21,58,59]. Based on these calculations, a minimum sample size of 157 participants, equally divided over 5 treatment locations, will be required.

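### The 157 patients for 95% power do not follow from the section's own inputs: the inflation factor fits about 9.6 patients per location where 31.4 are planned, and location is not the unit that needs inflating

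*Protocol article*

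**What the plan says.** The Sample Size Calculation section of the protocol article uses a repeated-measures analysis of variance with "within-factor time (5 levels) and between-factor treatment (2 levels) conditions on the outcome variable PDI". It states "We have set the α to .05" and "the power (1 – β) to .95", with f = 0.2, described as moderate. It then inflates for dependency of patients within 5 locations, "assuming an intracorrelation coefficient of 0.2", and adds that "we corrected the analysis for an expected attrition of 20" per cent. The result is "a minimum sample size of 157 participants, equally divided over 5 treatment locations, will be required".

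Elsewhere:
- **Study Setting:** "Six treatment facilities that provide IMPT programs participate in this study", and six towns are listed. The abstract and the Outcomes section also count six.
- **Abstract, Methods:** "we plan to recruit 158 adult patients with chronic pain".
- **Randomization:** patients are randomised singly in individual programmes, and by therapy group where treatment is mainly given in groups.
- **Strengths and Limitations:** both conditions run inside the same centre.
- **Primary Analysis: Pain Disability:** treatment location is in the model.

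The section prints neither the sample size before inflation, nor the cluster size used in the inflation, nor the correlation between repeated measures.

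**The concern.** A variance inflation factor depends on the number of patients per cluster. The section ends with 31.4 patients in each location (157/5). If the factor was computed from a smaller cluster, the stated power does not follow from the stated ICC and number of locations.

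There is a second problem. A cluster-trial factor is meant for the unit that is randomised. Here locations contain both arms, and the unit that is randomised as a block, in group programmes, is the therapy group.

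The N, power and effect size in this section are what a reader will use to interpret a null result. If the text says 95% power for a moderate effect and that statement has no valid derivation, a null result may be taken to rule out more than it does.

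**Working it through.** **Inputs from the section:** α = 0.05, power 0.95, f = 0.2, 5 time points, 2 groups, ICC 0.2, 5 locations, attrition 20%.

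**Assumptions:** the tested effect is the time-by-treatment interaction, as in the primary analysis; correlation between repeated measures ρ = 0.5 with sphericity (neither is stated); inflation factor VIF = 1 + (m − 1) × ICC for m patients per cluster.

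**Step 1, reproduce 157.** The noncentral F has λ = f² × N × 5/(1 − ρ), with 4 and 4(N − 2) degrees of freedom. N = 47 gives power 0.947 and N = 48 gives 0.952, so the base size is 48.
- m = 48/5 = 9.6
- VIF = 1 + 8.6 × 0.2 = 2.72
- 48 × 2.72 = 130.6
- 130.6 × 1.2 = 156.7, rounded up to 157

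**Step 2, other routes to about 157.**
- ρ = 0.51, base 47, m = 9.4, VIF 2.68: 47 × 2.68/0.8 = 157.45.
- Six locations, ρ = 0.46, base 52, m = 8.7: 158.1 after ×1.2.
- The only nearby route that uses 31.4 per location has base 18 and ρ about 0.83: 18 × 7.08/0.8 = 159.3, which misses 157.

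So the routes that fit best all use about 9 patients per location.

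**Step 3, the same formula at the planned cluster size (5 locations, ρ = 0.5).**

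| Basis | m | VIF | Effective N | Power |
|---|---|---|---|---|
| 157 enrolled | 31.4 | 7.08 | 22.2 | 0.63 |
| 125.6 retained (157 × 0.8) | 25.1 | 5.82 | 21.6 | 0.61 |

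For the retained patients, power is 0.46 at ρ = 0.3, 0.85 at ρ = 0.7 and about 0.95 only at ρ = 0.78. As m grows, effective N approaches 5/0.2 = 25, so under this method no enrolment reaches 48. With six locations the cap is 30, and power with 125.6 retained is 0.69.

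**Step 4, attrition.** 130.6/0.8 = 163.2, so 164 would be needed, not 157. With VIF 2.72 kept, effective N is 125.6/2.72 = 46.2 and power is 0.943.

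**Step 5, the unit that is randomised.** Drop the location inflation and take 126 completers (158 × 0.8 = 126.4), f = 0.2, ρ = 0.5. With no clustering, power exceeds 0.999. If every patient were in a therapy group of size g (not stated, so assumed) at ICC 0.2, the design effect is 1 + (g − 1) × 0.2:

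| g | Design effect | Effective N | Power at f = 0.2 |
|---|---|---|---|
| 4 | 1.6 | 78.8 | 0.998 |
| 6 | 2.0 | 63.0 | 0.989 |
| 8 | 2.4 | 52.5 | 0.968 |
| 10 | 2.8 | 45.0 | 0.937 |

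These figures also depend on ρ. At g = 10 the same formula gives 0.82 for ρ = 0.3 and above 0.99 for ρ = 0.7.

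**Step 6, what f = 0.2 means.** With arm differences d over the five visits in SD units, f is half the standard deviation of those differences over time.
- (0, d, d, d, d): f = 0.2d, so d = 1.0 SD
- (0, 0, d, d, d): f = 0.245d, so d = 0.82 SD
- (0, 0, d/4, d/2, d): f = 0.187d, so d = 1.07 SD at 12 months

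For an assumed PDI standard deviation of 11 to 15 (not in the article), this is 0.82 × 11 = 9 to 1.07 × 15 = 16 points. A difference of 0.5 SD at all four later visits is f = 0.1. With 126 completers, all in groups of 8 at ICC 0.2, its power is 0.41.

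**The case against.** The strongest objection is that a power of 0.61 does not describe this trial. Both arms sit inside each location and location is in the model, so differences between locations largely drop out of the treatment comparison. A reader might infer from Step 3 that the trial is underpowered for its stated effect. The documents do not support that: with the matching correction, power at f = 0.2 and ρ = 0.5 is above 0.999 without clustering and falls below 0.95 only for larger therapy groups. Even those figures are cautious, because they put every patient in a group while the Randomization section also allocates individuals. This objection stands in full. Step 3 tests only whether the section's conclusion follows from its own method.

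The cluster size of 9.6 is inferred, since the article prints neither 48, 2.72 nor ρ. That is fair, but the match to 157 is exact and the close alternatives use about the same cluster size. The ×1.2 for attrition is less certain, because one route reaches 157.45 with /0.8. It matters little either way, and the multilevel model keeps the partial data of patients who drop out.

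The difference between 157 and 158 is not an error: 158 meets a stated minimum and is the next even number for 1:1 allocation.

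The translation into PDI points rests on assumed standard deviations. The article's 8.5 to 9.5 points are described as an important change, not as a difference between arms, and the low end of the translated range falls within them. So the finding is not that the target effect is implausible, only that the word moderate is unexplained.

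**Conclusion.** The concern holds as a fault in the derivation. The stated 95% power at 157 patients does not follow from the section's own ICC, number of locations and final size: the inflation factor matches about 9.6 patients per location instead of 31.4. Used consistently, the formula gives an effective N of about 22 against 48 needed, and power of about 0.61 at ρ = 0.5 (0.46 at ρ = 0.3, 0.85 at ρ = 0.7).

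The inflation is also attached to the wrong unit, the therapy group receives no allowance, and 5 locations contradicts six. The attrition step is probably wrong by a small amount.

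None of this shows that 158 patients are too few for f = 0.2. It does show that the printed justification cannot support a claim of 95% power for a moderate effect, since f = 0.2 here means roughly 0.8 to 1.1 SD and power is lower for smaller differences. The power figures assume sphericity, the stated values of ρ and, for Step 5, group sizes that the article does not give. Like the section's own method, they apply the ICC directly to the interaction test.

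**What to change.** Keep enrolment at 158 and rewrite the Sample Size Calculation section so that it:

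1. uses six locations, in agreement with Study Setting;
2. drops the location-level inflation and says why (both arms within each location, location in the model);
3. applies a design effect of 1 + (g − 1) × ICC to the group-randomised share only, stating that share, g and the ICC;
4. states the assumed correlation between repeated measures and the sample size before inflation;
5. applies attrition as N/(1 − 0.2);
6. expresses f = 0.2 as a PDI difference with its assumed standard deviation and time pattern, and drops or justifies the word moderate;
7. reports power over a range of g, ICC and correlation, for f = 0.2 and for at least one smaller difference, in place of a single 0.95.

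Enlarging the trial to satisfy a location-level factor would not work, because at ICC 0.2 the effective N is capped at 25 or 30. The cost is text only: no extra patients and no change to the analysis. Since recruitment has started, the rewritten section should be presented as a restated justification of the planned size.

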#### Primary Analysis: Pain Disability

In our primary analysis, we will test the difference in the development of pain disability over time between patients in the enhanced condition and patients in the treatment condition. To account for the assumed dependence of the repeated observations and treatment locations, we will perform a multilevel analysis. In our hierarchical model, time points (level 1) will be nested in patients (level 2) and patients nested in treatment locations (level 3). Our main analysis will include the effects of time, treatment condition, treatment location, and the interaction between time and treatment condition, with a random intercept for patients. In addition, the model will be adjusted for sex, age, pain intensity, and pain duration. In the case of a significant 2-way interaction between time and treatment condition, posthoc contrasts between the treatment conditions at 3, 6, and 12 months will be calculated. We will also perform a subgroup analysis for patients that report a positive treatment effect at t_1_ (ie, a GPE score of 1 or 2).

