### Data Analysis

During all analyses, the treatment condition will be masked to the researchers. We will analyze the data according to the intention-to-treat principle and include patients in the analysis regardless of their adherence to the treatment protocol. We will perform no interim analysis. We will collect data at the following time points: –t_1_ (baseline), t_1_ (immediately postintervention), t_2_ (3 months postintervention), t_3_ (6 months postintervention), and t_4_ (12 months postintervention). Prior to the main analysis, we will check the randomization by examining the distribution of baseline characteristics between both groups.

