### Participant Timeline

Patient eligibility screening, informed consent, and treatment allocation procedures, as well as the baseline assessment, will be completed prior to the start of the treatment program. Patients in the enhanced treatment condition will receive instruction on how to download and use the app, and both strategies will be explained by a member of the treatment staff. To match the existing treatment content and procedures, the moment that the app will be introduced to patients can vary between locations. During the treatment phase, the app is considered a supplement to the main treatment activities and patients are free to decide how and when to use the app. Health care providers will be instructed to encourage and facilitate using the strategies when they expect it will reinforce the treatment process. However, both strategies can largely be used independently of any treatment activity and are expected to minimally affect direct treatment time. A member of the research team will be available to the treatment staff throughout the experimental phase for additional questions, support, and discussions regarding optimal use. Following treatment, there will be no additional monitoring in the enhanced treatment condition. Patients will continue to be able to use the app at their discretion. Posttreatment data will be obtained directly posttreatment (t1), and at 3 months (t2), 6 months (t3), and 12 months (t4) posttreatment.

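### A random intercept alone imposes equal variances and correlations over five unequally spaced visits, and can misstate the standard errors of the primary time-by-treatment test

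*Protocol article*

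**What the plan says.** The Primary Analysis section of the protocol article describes a three-level model: time points within patients within treatment locations. Main effects of time, condition and location are listed first. The sentence that lists them ends by adding "the interaction between time and treatment condition, with a random intercept for patients". Sex, age, pain intensity and pain duration are added as covariates. No random effect of time, residual correlation structure or robust standard error is mentioned.

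The interaction is the primary test, and it also decides whether visit-specific results are computed: "In the case of a significant 2-way interaction between time and treatment condition, posthoc contrasts between the treatment conditions at 3, 6, and 12 months" are to be calculated.

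The Data Analysis section lists five time points: baseline, end of treatment, and 3, 6 and 12 months after treatment. Under Participant Timeline, eligibility, consent and allocation, "as well as the baseline assessment, will be completed prior to the start of the treatment program". The series therefore spans 12 months plus the length of the programme, with unequal gaps. The Sample Size Calculation rests on a "2-factor repeated-measures analysis of variance with within-factor time (5 levels) and between-factor treatment (2 levels) conditions", with no stated correlation between visits and no allowance for unequal correlations.

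**The concern.** A patient intercept with independent residuals implies compound symmetry. The score before treatment must then correlate with the 12-month score exactly as strongly as the 3-month score does with the 6-month score, and the spread between patients must be the same at every visit. A random intercept for location would not relax this, because it is also constant over time.

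The design speaks against both conditions. An intensive programme separates the first visit from the rest, the later gaps are 3, 3 and 6 months, and the trial is about how patients hold or lose their gains. The Strengths and Limitations section itself expects functional status to fluctuate after treatment.

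At stake is the calibration of the primary test and of the contrasts that follow from it. This is a choice that the text makes, so an analysis plan that followed the sentence as written would inherit it.

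**Working it through.** **The plan's own figure.** For the interaction of a repeated-measures analysis of variance with f = 0.2, 5 visits, alpha 0.05 and power 0.95, with an assumed correlation of 0.5 (not stated) and sphericity (epsilon = 1), 48 patients are needed (power 0.952). The design effect is 1 + (48/5 - 1) x 0.2 = 2.72; 48 x 2.72 = 130.6; x 1.2 for attrition = 156.7, so 157. By this route the stated 157 carries no allowance for unequal correlations. With 20% attrition, 157 x 0.8 = 125.6, so about 126 patients, or 63 per arm, are used below.

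**What the model assumes.** With intercept variance T and residual variance R, every visit has variance T + R and all 10 pairs of visits have correlation T/(T + R). If the true pattern differs:

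- R is estimated as (mean variance) - (mean covariance) over the visits. The model variance of a within-patient change is 2R; the true one is v_i + v_j - 2c_ij.
- The model variance at a single visit is the mean of the five variances; the true one is v_j. An arm contrast at one visit therefore does not depend on how correlation decays.

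**Example 1, decaying correlation.** Assume constant variance 1, correlation 0.8 per 3 months and visits at -3, 0, 3, 6 and 12 months (programme length assumed). The 10 correlations sum to 3(0.8) + 3(0.64) + 2(0.512) + 0.4096 + 0.3277 = 6.081, mean 0.608, so R = 0.392.

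- 12 months minus end of treatment: model 0.784, true 2(1 - 0.4096) = 1.181, SE ratio sqrt(0.784/1.181) = 0.81. The SE is too small.
- 3 months minus end of treatment: true 2(1 - 0.8) = 0.4, SE ratio sqrt(0.784/0.4) = 1.40. The SE is too large.
- Arm difference at any visit: model 1, true 1, ratio 1.

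**Example 2, only baseline correlates weakly.** Assume 0.3 with baseline and 0.7 among the other visits. The mean correlation is (4 x 0.3 + 6 x 0.7)/10 = 0.54, so R = 0.46. For 12 months minus end of treatment: model 0.92, true 0.6, ratio 1.24. This contrast is conservative.

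**Example 3, growing variance.** Assume patient slopes with SD 0.05 per month (in units of the starting SD), independent of the intercept, from a programme start at -4 months. The variances are 1 + 0.0025 x (0, 16, 49, 100, 256) = 1, 1.04, 1.1225, 1.25, 1.64, mean 1.2105. At 12 months the SE ratio is sqrt(1.2105/1.64) = 0.86.

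**Simulated type I error** (63 per arm, complete data, time categorical, nominal 5%; contrasts not gated on the interaction; ranges combine separate runs; a dash means not simulated):

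| Assumed pattern | Time-by-treatment | Arm contrast at 12 months | 12 months minus end of treatment |
|---|---|---|---|
| Equal correlation 0.5 or 0.7 | 4.7-4.9% | - | 4.9-5.0% |
| Decay 0.95 per month | 7.4% | 5.0-5.1% | 10.7-10.8% |
| Decay 0.90 per month | 6.7-7.5% | 4.8% | 9.8-10.2% |
| Decay 0.9, 0.8, 0.7 per 3 months | 8.0, 7.4, 6.9% | - | 12.0, 11.2, 10.2% |
| Stable patient part plus partial decay (0.4 + 0.6) | 6.1% | - | 8.9% |
| Random slopes, SD 0.03-0.05 per month | 4.9-5.8% | 5.8-9.3% | - |
| Baseline 0.3-0.5, other visits 0.7 | 5.9-6.6% | - | 2.7-1.5% |

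The per-month rows place baseline at -4 months and the decay-per-3-months and weak-baseline rows at -3. Under decay, the arm contrasts at 3 and 6 months lay between 4.6% and 5.2%. An unstructured covariance under 0.95 decay gave 4.9% for the interaction and 4.6% for the change from baseline to 12 months.

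**The case against.** The strongest reply is that the article names a random intercept but does not say that residuals are independent. A residual correlation structure is compatible with a random intercept, and an analysis plan not shown may add one. That stands as a condition: everything here applies to the model as written with ordinary residuals. It does not dispose of the point, because the random part is stated and no safeguard accompanies it.

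Second, the effect on the primary test is modest and conditional. If correlations are equal, the test holds its level, and varying patient slopes alone barely move it. This also stands.

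Three stronger readings are tempting and are not supported:

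- A reader might infer that the standard errors are certainly too small. The documents give no correlations between visits, and Examples 1 and 2 show errors in both directions.
- A reader might carry the 10-12% rates over to the planned contrasts. Those rates belong to changes between visits. The planned contrasts, read literally, are arm differences at 3, 6 and 12 months. They keep their level under decay with constant variance and move only if variance changes over time.
- A reader might infer that the handling of incomplete data is biased, since the plan relies on the multilevel model for it. That depends on the dropout mechanism. In a check with 0.95 decay per month and 21% dropout driven by the 6-month score, the bias in the 12-month mean was -0.003 SD, which is negligible.

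**Conclusion.** The point holds in conditional form. As stated, the random part of the primary model is valid only under equal variances and equal correlations over five unequally spaced visits, which this design makes unlikely. The interaction test then has a type I error of about 5-8%. The 12-month arm contrast is near 5% under decay with constant variance and about 6-9% if variance grows. Change contrasts can be anticonservative or conservative.

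These figures rest on assumed correlations, an assumed programme length of 3 or 4 months, complete data and categorical time. The coding of time is not stated, although the five levels in the sample size section point to categorical. If time were linear, the slope-by-treatment test would be further off: about 16-20% under the three decay-per-3-months patterns and 8-10% with random slopes.

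This is worth correcting because it affects the primary test and costs little. It does not invalidate the trial.

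**What to change.** In the Primary Analysis section, state that time enters as a categorical factor, and replace the random-intercept-only structure with an unstructured within-patient covariance over the five visits. Use small-sample degrees of freedom (for example Kenward-Roger). Name a simpler fallback in case of non-convergence, such as a heterogeneous spatial-power structure or a random intercept plus random slope.

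The unstructured form has 5 variances and 10 covariances, 15 parameters in place of 2. About 126 patients with up to five visits each can support that. The change is one sentence, needs no new data, and should be made before unmasked data are analysed.

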### Study Objectives

The present trial has three main objectives. Our first objective is to evaluate the effectiveness of the AGRIPPA intervention (ie, enhanced treatment condition) on pain disability for patients with chronic musculoskeletal pain who participate in an IMPT program compared to a usual care control group with a follow-up period of 12 months. Our second objective is to determine the cost-effectiveness of the AGRIPPA intervention relative to usual care. Our third objective is to explore the level of engagement and perceived usability of patients that use the app. We have formulated three hypotheses: (1) the maintenance of improvement in pain-related disability over time after IMPT will be more favorable for the enhanced treatment condition compared to usual care; (2) the effect of the app on pain disability will translate to less health care utilization and less societal costs (eg, less absenteeism), leading to a cost-effective intervention compared to treatment as usual; and (3) for participants in the enhanced treatment condition, the perceived usability, frequency of use, duration of use, and reported adherence to the AGRIPPA app will be positively associated with a favorable change over time of pain-related disability.

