**Primary**				
	Self-perceived pain disability	The development of pain disability over time after IMPT^a^ will be more favorable for the enhanced treatment condition compared to usual care.	PDI^b,c^	Multilevel analysis
	Planned subgroup analysis on patients that scored 1 (“very much better”) or 2 (“much better”) on the GPE^d^ scale at *t*_1_^e^.	For patients that experienced meaningful treatment success, the development of pain disability over time after IMPT will be more favorable for the enhanced treatment condition compared to usual care.	1. PDI^c^ 2. GPE^f^	Multilevel analysis

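### The primary time-by-treatment test appears to include the pretreatment visit, so it is not specific to maintenance after treatment, and the gated follow-up contrasts make no use of baseline PDI

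*Protocol article*

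**What the plan says.** Hypothesis 1 in the protocol article (Study Objectives) is that "the maintenance of improvement in pain-related disability over time after IMPT will be more favorable for the enhanced treatment condition compared to usual care". Table 1, primary outcome, is worded the same way: "The development of pain disability over time after IMPT".

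Primary Analysis: Pain Disability specifies a multilevel model with "the effects of time, treatment condition, treatment location, and the interaction between time and treatment condition, with a random intercept for patients". On covariates, "the model will be adjusted for sex, age, pain intensity, and pain duration". The follow-up comparisons are conditional on that interaction being significant; only then, the section says, "posthoc contrasts between the treatment conditions at 3, 6, and 12 months will be calculated".

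That section does not say which visits enter the model. Two other sections bear on it:
- Data Analysis lists five visits: one before treatment (-t1), one at its end (t1), and three in follow-up (t2, t3 and t4 at 3, 6 and 12 months).
- Sample Size Calculation is built on "within-factor time (5 levels) and between-factor treatment (2 levels) conditions on the outcome variable PDI".

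Baseline PDI is a named covariate in the engagement regression (Perceived Usability and App Engagement) but not in the primary model. According to Outcomes, the PDI and the baseline measurements come from routine data collection.

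**The concern.** Maintenance is about what happens from t1 onward. An interaction over all five visits asks a wider question: do the arms differ in any part of their course, including the change during treatment? The Design section gives the experimental arm the app during treatment as well as after it, so the arms can separate before t1. A significant result could then come wholly from that early separation and be reported as better maintenance.

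The planned contrasts do not settle this. They compare arm levels at 3, 6 and 12 months, not change since t1, and they are calculated only once the gate is passed. They also leave baseline PDI unused. Under simple individual randomization and randomization of whole groups (Randomization section), chance imbalance in baseline PDI would pass into them.

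**Working it through.** **Step 1: which test does the sample size describe?** Inputs from Sample Size Calculation: f = 0.2, alpha 0.05, power 0.95, m = 5 time levels, 2 arms, intracluster correlation 0.2, 5 locations, 20% attrition. Assumed, because not stated: correlation between visits rho = 0.5 and sphericity.

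- Noncentrality for a within-between interaction: lambda = f² × N × m / (1 − rho). At N = 48: 0.04 × 48 × 5 / 0.5 = 19.2, with df 4 and 46 × 4 = 184. Power is 0.952.
- Inflation for location: 1 + (48/5 − 1) × 0.2 = 2.72, and 48 × 2.72 = 130.56.
- Attrition: 130.56 × 1.2 = 156.67, rounded up to 157, the stated figure.

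Among the variants tried, only this one gives 157. Four time levels with the same steps give 198 to 205. A between-arm main effect with 5 locations gives more than 2,000. Dividing by 0.8 instead of multiplying by 1.2 gives 164. The planned test is therefore best read as a 4-df interaction over all five visits, -t1 included.

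**Step 2: how does that test behave when maintenance does not differ?** Assumptions: N = 157 × 0.8 = 125.6, taken as 126 (63 per arm); compound symmetry; clustering ignored. With arm differences d_j in SD units, lambda = (N/4) × Σ(d_j − mean d)² / (1 − rho).

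Let the arms separate by 0.4 SD between -t1 and t1 and then run parallel: d = (0, 0.4, 0.4, 0.4, 0.4), mean 0.32.

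- Sum of squares: 0.32² + 4 × 0.08² = 0.1024 + 0.0256 = 0.128.
- 31.5 × 0.128 = 4.032, divided by (1 − rho); df 4 and 124 × 4 = 496.

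| rho | lambda | five-visit test significant | t1-t4 test significant |
|---|---|---|---|
| 0.3 | 5.76 | 45% | 5% |
| 0.5 | 8.06 | 60% | 5% |
| 0.7 | 13.44 | 85% | 5% |

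Over t1-t4 all four differences are equal, so lambda is 0 and the test holds its nominal level. With a separation of 0.3 SD the five-visit figures are 26%, 36% and 57%.

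The same scenario shows the effect of the gate. At rho = 0.5, a benefit of 0.4 SD that is present at every posttreatment visit leaves the follow-up contrasts untriggered in 100 − 60 = 40% of trials.

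**Step 3: what does leaving out baseline PDI cost the contrasts?** Adjustment multiplies the variance of a single-visit difference by 1 − rho²: 0.91, 0.75 and 0.51 at rho 0.3, 0.5 and 0.7. For a 0.4 SD difference with 63 per arm (normal approximation), power rises from 61% unadjusted to 65%, 74% and 88%.

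**Step 4: what would a t1-t4 test cost?** Let a maintenance effect grow in equal steps by visit from 0 at t1 to 0.4 SD at t4, with rho = 0.5.

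- Five visits: d = (0, 0, 0.133, 0.267, 0.4), mean 0.16, sum of squares 0.1209; lambda = 31.5 × 0.1209 / 0.5 = 7.62; power 58%.
- t1-t4: mean 0.2, sum of squares 0.0889; lambda = 5.60, df 3 and 372; power 48%.
- One-df contrast of t4 minus t1: lambda = 31.5 × 0.16 / (2 × 0.5) = 5.04; power 61%.

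**The case against.** The strongest reply is that inclusion of -t1 is inferred. Primary Analysis lists no visits, and reference visit and contrast coding usually belong in an analysis plan, which is not shown. That stands as a caveat. However, the sample size section fixes five levels, the schedule has exactly five visits, and nothing in the article limits the primary model to t1-t4. If -t1 were in fact left out, the primary model would contain no baseline PDI at all, so the adjustment point holds on either reading.

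A reader might go further in three ways that the documents do not support.

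- *The primary test does not test the hypothesis.* This is too strong. The five-visit interaction has real power for a maintenance effect (58% in Step 4, against 61% for the t4 minus t1 contrast). With -t1 among the outcomes, it already compares changes and so accounts for baseline level. The fault is lack of specificity.
- *A benefit seen only at t1 shows that the test fires without a maintenance difference.* It does not. Arms that differ at t1 and then converge have a different course after treatment, and a t1-t4 interaction would detect that too. The contrasts at 3, 6 and 12 months would also show no benefit.
- *The primary test should be the baseline-adjusted average over t2-t4.* That average measures level, not change since t1. In the parallel scenario of Step 2 (0.4 SD, rho = 0.5) it is significant in 93% of trials, so it is less specific to maintenance than the planned test. It also has no power advantage when the arms diverge gradually: 52% against 54% for differences of 0, 0.1, 0.2 and 0.4 SD at t1 to t4.

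It is also true that randomization leaves the unadjusted contrasts unbiased on average. Their cost is lost precision and exposure to chance imbalance.

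**Conclusion.** The concern holds in a limited form. As best read from the article, the primary test covers the pretreatment visit and cannot separate better maintenance from a difference formed during treatment. With no difference after t1 and a 0.4 SD separation before it, the test is significant in about 60% of trials (45% to 85% for rho 0.3 to 0.7), where a posttreatment test would give 5%. These figures assume 63 per arm, compound symmetry and no clustering. The correlation and the size of the separation are not in the documents.

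The contrasts at 3, 6 and 12 months are gated and not adjusted for a baseline PDI that is already collected. Adjusting them would cut their variance by 9% to 49% over the same range of correlations (1 − 0.91 to 1 − 0.51). This part does not depend on which visits are in the model.

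**What to change.** 1. Constrain the arms to a common mean at -t1, or use -t1 PDI as a covariate with t1-t4 as outcomes, so that the 3, 6 and 12-month differences are baseline-adjusted. Report them with confidence intervals whether or not the interaction is significant.
2. State which visits enter the primary test and make it match the hypothesis: either restrict the time-by-treatment test to t1-t4, or prespecify a contrast of change since t1. Report the -t1 to t1 difference between arms separately, as the during-treatment effect. The five-visit interaction can stay as a supportive analysis.
3. If the sponsor's target is the posttreatment level rather than change since t1, say so. An average over t2-t4 would suit that estimand, and the hypothesis should then be reworded to match.

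This changes analysis wording only and needs no new data. The price is some power for a gradually growing effect: about 48% against 58% in Step 4. A prespecified t4 minus t1 contrast avoids that loss in the same scenario (61%) but relies on a single follow-up visit. The stated power of 95% was worked out for the five-level test and should not be carried over to a four-level one, for which the same steps give 198 to 205 patients with f held at 0.2.
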